### Interim analyses {21b}

No interim analyses are planned.

### Methods for additional analyses (e.g. subgroup analyses) {20b}

The progression of the abovementioned parameters, between 3 and 6 or 12 months, in patients with or without OSAS treatment will be compared using a mixed model. Interactions between visit, group and treatment for OSAS will be investigated. The model will also be adjusted for the centre (random effect).

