## Introduction

### Background and rationale {6a}

Nonarteritic anterior ischaemic optic neuropathy (NAAION) is the most frequent acute optic neuropathy after 50 years of age, with a general annual incidence worldwide of 10 per 100,000 individuals, and estimated at 6000 cases/year in France [1]. The pathophysiology of the disease is not well understood, being probably related to acute hypoperfusion in the short posterior ciliary arteries resulting in damage to the papillary microcirculation. This condition has been associated with various predisposing systemic factors [2] such as obstructive sleep apnoea syndrome (OSAS) in 75–80% cases [3–6], hypertension in 38–60% [7–10], diabetes in 12–23% [7, 8], dyslipidemia in 36–48% [10, 11] and anatomic ocular factors (small papillary excavation [12–15]).

The prognosis of NAAION is most often unfavourable, due to the irreversible loss of central visual acuity and visual field (VF). While some studies have reported slight spontaneous improvement (22%) [16], others reported no improvement or the deterioration of visual acuity (VA) or the VF [9, 17]. In eyes initially presenting minimum to slight VF defects, worsening was observed at 3 months after the first visit in 26% of cases and at 2 years in 27% of cases [16].

It is crucial to develop new therapeutic strategies for the acute stage of the disease so as to reduce optic nerve damage. Although corticosteroids and levodopa have been tried, these treatments have not been fully validated [18–23]. Other therapeutic strategies have been proposed, but their efficacy has not been demonstrated. These include posterior vitrectomy in patients with a small optic nerve head (ONH) and partial posterior detachment of the vitreous [24], radial neurotomy [25], intravitreal injection of triamcinolone [26, 27], electrical transcorneal stimulation [28], instillation of brimonidine [29] and LDL apheresis [30]. No validated treatment currently exists for this ischaemic optic neuropathy. Table 1 summarises the main recent studies on NAAION treatments.

**Table 1 Tab1:** Summary of studies on the treatment of NAAION (2008–2020)

Author (year)	Grade of evidence	Number of patients	Type of study	Treatment window (range)	Treatment (dose)	Outcome	Confounding factors considered

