Among novel strategies aimed at treating NAAION, treatment with a systemic endothelin receptor antagonist has recently emerged as a promising new strategy, for the following reasons:NAAION is associated in 75–80% of cases with OSAS [47–49]. The endothelin system is activated in OSAS patients, and endothelin 1 (ET-1) is associated with intermittent hypoxia, a major feature of OSAS [50, 51]. It is also involved in the physiopathology of cardiovascular disease (hypertension, myocardial infarction and/or vascular remodelling, all frequent comorbidities of OSAS).Endothelin 1 is implicated in vascular damage of the optic nerve. In animal models, the application of ET-1 directly to the optic nerve, or in the eyes, induces ischaemic optic neuropathy. An increase in the plasma levels of ET-1 was also found in NAAION patients [52].At the ocular level, bosentan, a duel ET-1 receptor antagonist, increases retinal and optic nerve blood flow in healthy humans and glaucoma patients [53].Bosentan is an already certified medication used in pulmonary arterial hypertension, and for digital ulcers associated with systemic sclerodermia, and has a good tolerance profile. While abnormally high levels of hepatic enzymes occur in approximately 10% of patients, with 3% of them discontinuing treatment, any hepatic toxicity can be easily detected [54].

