### Eligibility criteria {10}

NAAION is diagnosed based on the standard criteria of recent (≤ 21 days), rapid and painless onset of VF loss, occurring with diffuse or sectorial swelling of the optic disc [56]. The trial’s inclusion and non-inclusion criteria are listed in Table 2. In each participating centre, possible differential diagnoses are carefully assessed by physicians with expertise in neuro-ophthalmology.

**Table 2 Tab2:** Inclusion and non-inclusion criteria

Inclusion criteria	Non-inclusion criteria
Age ≥ 50 years old	Pregnant or breast-feeding women^a^
Patients who signed the consent form	Patients with other acute or chronic intercurrent ocular pathology interfering with visual acuity or visual field (diabetes, drug-induced or other retinopathy, other optic neuropathy including uni- or contralateral glaucoma and/or intraocular pressure > 30 mmHg, advanced cataract, corneal opacities, amblyopia < 5/10, severe myopia > −6 diopters, retinal disease)
Patients affiliated with a national health insurance scheme or beneficiaries of such a scheme.	Simultaneous bilateral NAAION, occurring 1 month apart or less
	Evidence or suspicion of other causes of optic neuropathies considered as main differentials: 1/ giant cell arteritis causing arteritic anterior ischemic optic neuropathy (AAION) 2/ Optic neuritis (based on clinical examination, personal history of multiple sclerosis, contributive ancillary investigations) and 3/ compression/infiltration of the optic nerves, based on the clinical findings and orbital/brain imaging.
	Patients with systolic blood pressure below 100 mmHg
	Patient with orthostatic hypotension (20 mmHg drop in SBP and/or 10 mmHg drop in DBP when moving to a standing position)
	Neurological history of vascular or tumour-related changes to the visual field or other optic neuropathy
	Systemic inflammatory disease
	Known allergy to bosentan
	Patients with moderate to severe hepatic impairment (Child-Pugh class B or C), biliary cirrhosis (serum levels of liver aminotransferases, aspartate aminotransferases (ASAT) and/or alanine aminotransferases (ALAT), greater than three times the upper limit of normal, bilirubin greater than twice normal)
	Estimated glomerular filtration rate (GFR) < 30 ml/min/1.73 m^2^
	Patients treated with drugs whose efficacy may be reduced by activation of cytochrome P450, 2C9, 3A4 and 2C19 isoenzymes
	Patients treated with amiodarone

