**Fig. 2 Fig2:**
[figure not shown]
Schedule of enrolment, interventions and assessments for a patient included in the ENDOTHELION trial

Following randomisation, the first administration of the treatment is given in the ophthalmology department. Blood pressure (BP) is checked 4 h after this, corresponding to the plasma peak of bosentan according to the pharmacological data in the study by Weber et al. [59].

Patient monitoring/follow-up includes consultations at week 2, and at 1, 2, 3, 6, 12 and 24 months with one of the investigating ophthalmologists, during which several examinations are carried out: an ophthalmological examination (VA, VF, SD-OCT and fundus examination), a clinical examination searching for the adverse side effects of bosentan, an office-measurement of BP and a blood work-up including a haemogram and measurement of liver enzymes (until and including the month 2 visit). Self-measurement of BP is programmed during weeks 1 and 4 and the last week of treatment (week 8).

The primary endpoint is set at 3 months so as to assess the efficacy of bosentan before initiating treatment for OSAS, the recognised period when visual function usually stabilises, and papillary oedema disappears, proceeding to papillary atrophy. Contreras et al. [60] showed that at 1.5 months following the acute phase, the RNFL thickness of the affected eye was similar to that of the unaffected eye, indicating that the optic disc swelling had partly resolved. After this first period, atrophy of the optic nerve head became detectable, such that at the 3-month visit, the RNFL had thinned by 39%, compared to the contralateral normal eye [60]. Loss of retinal nerve fibre layers stabilised thereafter, with only 6% additional thinning at the 12-month visit. In another study, Hayreh et al. [57] estimated the median time to papillary oedema resolution was 7.9 weeks (IQR, 5.8–11.4 weeks).

In the present trial, at 3 months, the clinical examinations and laboratory analyses (including a study of endothelial function), the ophthalmological examinations (VA, VF, SD-OCT and fundus examination) and the blood work-up (with serum banking) performed at inclusion are repeated. A polysomnography is planned after the 3-month visit.

The visits at 6 and 12 months and the end-of-protocol visit at 24 months include an ophthalmological examination (VA, VF, SD-OCT and fundus examination). The quality-of-life questionnaire (VFQ-25) [58] is completed at the 3- and 12-month visits.

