Alternative approaches are to *improve ocular perfusion conditions at the optic nerve* through LDL apheresis or bosentan treatment. *LDL apheresis* selectively eliminates fibrinogen, LDL, cholesterol, triglycerides and LP from plasma using extracorporeal circulation. This can reduce fibrinogen and LDL by approximately 50% after a single procedure and immediately improves haemorrhagic status [77]. In a 3-month prospective, randomised, controlled trial [78], 40 NAAION patients underwent heparin-induced extracorporeal fibrinogen or LDL precipitation (HELP) treatment, haemodilution or intravenous perfusion of pentoxifylline. While no significant difference was found between the two HELP and the haemodilution groups for VA, a 2-line or greater improvement was obtained in 47% of the HELP group, 10 (52.6%) remained stable and none worsened. In the haemodilution group, VA increased in seven patients (33%), nine (42.8%) remained stable and five (23.8%) experienced a decrease. The mean calculated VF sensitivity improved significantly (*P* < 0.01) in the HELP group, increasing from 6.83 ± 4.52 dB to 8.27 ± 4.89 dB, but was not significantly changed in the haemodilution group (6.25 ± 4.12 dB to 6.12 ± 3.92 dB). The change in mean differences of the two groups was significant (*P* < 0.005).

The *endothelin receptor antagonist* bosentan increases retinal blood flow at the optic nerve head in healthy humans and glaucoma patients [53, 79]. Endothelin is also strongly implicated in cardiovascular disorders (hypertension, infarction, vascular remodelling) and the intermittent hypoxia due to OSAS, present in 70–85% of patients with NAAION [3–6]. This suggests that bosentan is a good candidate to reduce the vasoconstricting effect of endothelin in the acute phase of NAAION and may improve optic nerve perfusion conditions.

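### The OSAS-treatment comparison, as worded, does not separate patients without OSAS from patients with untreated OSAS, so it mixes treatment with disease status

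*Protocol article*

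**What the plan says.** The analysis is set out in the protocol article under Methods for additional analyses {20b}. Progression of the outcome measures between month 3 and months 6 or 12 "in patients with or without OSAS treatment will be compared using a mixed model". The section adds: "Interactions between visit, group and treatment for OSAS will be investigated". It then states: "The model will also be adjusted for the centre (random effect"). The named terms are therefore visit, randomised group, OSAS treatment, their interactions, and centre.

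Other sections bear on who falls into each group:

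- **Entry.** The inclusion criteria in Table 2 are age ("Age ≥ 50 years old"), consent and health insurance. OSAS is not required.
- **Prevalence.** Background and rationale {6a} says "NAAION is associated in 75–80% of cases with OSAS". The Discussion gives a wider range, "present in 70–85% of patients with NAAION".
- **Choice of OSAS treatment.** Relevant concomitant care {11d} allows CPAP to begin after the month-3 visit where it is needed. It is not randomised.
- **OSAS status.** Participant timeline {13} states: "A polysomnography is planned after the 3-month visit".
- **OSAS as a covariate.** Statistical methods {20a} adjusts for presence of OSAS only in the second model of change from baseline to month 3.

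**The concern.** Patients treated for OSAS have OSAS. On the plain wording, patients without OSAS treatment are of two kinds: those who do not have the disease, and those who have it but are not treated. If the two kinds progress differently after month 3, the comparison picks up that difference and shows it as a difference by treatment. It could hide a benefit of OSAS treatment or suggest one that does not exist.

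The article's own rationale makes this plausible. It links OSAS to the endothelin system on which bosentan acts, so equal progression, or equal response to bosentan, cannot be taken for granted. Participant timeline {13} also places the primary endpoint before OSAS treatment begins, so the authors regard that treatment as a possible influence on outcome.

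The planned interactions raise a second issue. OSAS treatment is chosen after randomisation, so bosentan–placebo contrasts within OSAS-treatment strata do not have the protection of randomisation. The section does not label the analysis as non-randomised.

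**Working it through.** **Inputs from the article.** The total is N = 86 (Sample size {14}). OSAS prevalence is p = 75–80% (Background {6a}) or 70–85% (Discussion). The share u of OSAS patients who receive treatment is not given; 25–75% is assumed here, with 100% as the limiting case.

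**The plan's own figure.** The article states no figure for this comparison; the sample size supplies only the head count. That figure reproduces closely. With a difference of 6 dB and an SD of 9 × √(1 − 0.3) = 7.53, two-sided alpha 0.05 and 90% power, the normal approximation gives 34 per group against the stated 36. Then 36 × 2 + 14 = 86.

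**Step 1: patients without OSAS.** N × (1 − p):

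- p = 80%: 86 × 0.20 = 17.2
- p = 75%: 86 × 0.25 = 21.5

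**Step 2: their share of the group without OSAS treatment.** s = (1 − p) / [(1 − p) + p(1 − u)]:

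| u (assumed) | p = 80% | p = 75% |
|---|---|---|
| 25% | 0.20 / (0.20 + 0.60) = 25% | 0.25 / (0.25 + 0.5625) = 31% |
| 50% | 0.20 / (0.20 + 0.40) = 33% | 0.25 / (0.25 + 0.375) = 40% |
| 75% | 0.20 / (0.20 + 0.20) = 50% | 0.25 / (0.25 + 0.1875) = 57% |
| 100% | 100% | 100% |

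With the wider prevalence range and u = 25–75%, s runs from 0.15 / (0.15 + 0.6375) = 19% to 0.30 / (0.30 + 0.175) = 63%. If every OSAS patient is treated, treatment and disease coincide and cannot be told apart.

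**Step 3: what this could do to the contrast.** Suppose OSAS treatment has no effect, treated and untreated OSAS patients progress alike, and patients without OSAS differ from them by D dB. The apparent treatment difference is then s × D. At p = 75–80% and u = 25–75%, that is 0.25 to 0.57 dB for each 1 dB of D, and the full 1 dB if u = 100%. The article gives no value for D.

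**Step 4: patients left after restriction to OSAS.** N × p: 86 × 0.75 = 64.5 and 86 × 0.80 = 68.8, so about 64–69.

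**The case against.** The strongest reply is that this is a short passage on an exploratory analysis in a condensed article. The wording can be read as treated versus untreated OSAS patients, and a full protocol or analysis plan, not shown, may define it so. That reading is possible but not written. The article does state the contrast, the interactions and the centre effect, and what it states does not separate the two kinds of untreated patient. The point stands as one about wording.

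Several stronger readings are tempting, and the article does not support them:

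- **That the model adjusts for nothing but centre.** It also contains visit, randomised group and interactions. What is not named is OSAS presence or severity.
- **That the result would have no meaning.** It would be a descriptive, non-randomised difference in progression. No objective in {7} or endpoint in {12} claims an effect of OSAS treatment.
- **That the comparison starts at the wrong time, or that OSAS treatment enters the randomised comparisons.** The analysis already begins at month 3, and the comparisons in {20a} contain no OSAS-treatment term.
- **That bias has been shown.** The percentages above describe who is in the group. Distortion also requires OSAS status to change progression after month 3, and the article has no figure for this. Participant timeline {13} describes visual function as usually stable by then, with only 6% further RNFL thinning by month 12, which would limit D. Sample size {14} reports some worsening of mean deviation between months 3 and 6, so D need not be zero.

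It is also fair to say that restriction to OSAS patients does not isolate a treatment effect. Treatment is given according to need, so confounding by indication remains.

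**Conclusion.** The point holds as a limited one. As worded, the analysis mixes OSAS treatment with OSAS status. About 17–22 of 86 patients would have no OSAS at the article's 75–80% prevalence. They would form about 25–57% of the group without OSAS treatment, or 19–63% at 70–85% prevalence. Both shares rest on the assumed uptake of 25–75% and on reading the sentence as it stands. The size of any resulting distortion in dB is unknown.

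The issue is confined to one exploratory analysis. The primary comparison and the listed secondary bosentan–placebo comparisons are untouched. The change is still worth making before unblinding, because it needs only wording and the planned polysomnography supplies the information.

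**What to change.** Amend {20b} in three respects:

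1. Define the comparison among patients with OSAS on the planned polysomnography. Alternatively, replace the two groups by a three-level factor: no OSAS, OSAS untreated, OSAS treated.
2. Adjust for OSAS severity as measured by the polysomnography.
3. Label the comparison, and its interaction with randomised group, as exploratory and non-randomised. State that OSAS treatment is chosen after randomisation and that confounding by indication remains.

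The cost is a change of text. If the comparison is restricted, about 64–69 of 86 patients remain, before any loss to follow-up. The three-level factor keeps everyone, with the comparison of interest then being treated versus untreated OSAS.

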### Methods in analysis to handle protocol non-adherence and any statistical methods to handle missing data {20c}

All available data will be included in the final mITT analysis, even in case of protocol non-adherence. However, missing data will not be replaced.

### Plans to give access to the full protocol, participant-level data and statistical code {31c}

After publication of the trial results, the dataset will be made available to the research community on reasonable request to the corresponding author. This will be the object of a contract with the sponsor.

**Coordinating center for the study: Grenoble Alpes University Hospital ([name])**	

### Composition of the data monitoring committee, its role and reporting structure {21a}

The data and safety monitoring committee DSMB) comprises [name] (Pharmacology department at the Grenoble-Alpes University Hospital, Grenoble, France), [name] (Department of ophthalmology, Bicêtre Hospital, Paris, France) and [name] (Department of ophthalmology, Dijon University Hospital, Dijon, France). The DSMB will be convened in the event of an unexpected serious adverse event or in case of unusual (in terms of frequency of onset) serious adverse events, at the request of the sponsor’s pharmacovigilance manager, and also at the trial’s halfway mark (17 March 2021) to assess any safety issues related to the trial. Unblinding can be requested by this board, without the investigator or the patient gaining knowledge of the treatment allocation. Meetings will be in closed session and independent of the investigators. The DSMB can also propose to the sponsor and the coordinating investigator that the study be discontinued or request that the protocol be modified if the security of the patients is deemed insufficient.

### Adverse event reporting and harms {22}

The known adverse effects of bosentan as well as their frequency are presented in Table 6.

**Table 6 Tab6:** Adverse events and their frequency for bosentan

Organ class	Frequency	Adverse event
**Haematologic and lymphatic system disorders**	Frequent	Anaemia, decreased haemoglobin level
	Infrequent	Thrombocytopaenia^a^ neutropenia, leucopenia^a^
	Undetermined frequency^a^	Anaemia or decreased haemoglobin level requiring blood transfusion^a^
**Immune system disorders**	Frequent	Hypersensitivity reactions (including dermatitis, pruritis and skin rash)^b^
	Rare	Anaphylaxis and/or angioedema^a^.
**Nervous system disorders**	Very frequent	Headaches^c^
	Frequent	Syncope^a,d^
**Ocular disorders**	Undetermined frequency	Blurred vision
**Cardiac disorders**	Frequent	Palpitations^a,d^
**Vascular disorders**	Frequent	Vasomotor symptoms, hypotension^a,d^
**Respiratory, thoracic and mediastinal disorders**	Frequent	Nasal congestion^a^
**Gastro-intestinal disorders**	Frequent	Gastro-oesophageal reflux, diarrhoea
**Hepatobiliary disorders**	Very frequent	Liver enzymes abnormality
	Infrequent	High liver aminotransferases associated with hepatitis (including possible aggravation of underlying hepatitis) and/or jaundice^a^
	Rare	Liver cirrhosis, liver failure^a^
**Skin and subcutaneous tissue disorders**	Frequent	Erythema
**General disorders and abnormalities at administration site**	Very frequent	Oedema, sodium and water retention^e^

^a^Data from post-marketing authorisation of bosentan, frequencies are based on the statistical model of the clinical trial with controls versus placebo

^b^Hypersensitivity reactions have been reported in 9.9% of patients taking bosentan and 9.1% of patients on placebo

^c^Headaches have been reported in 11.5% of patients on bosentan and 9.8% of patients on placebo

^d^These types of reactions can also be caused by the underlying disease

^e^Edemas or water/sodium retention have been reported in 13.2% of patients on bosentan and 10.9% of patients on placebo

Since market authorisation, rare cases of liver cirrhosis have been reported after prolonged bosentan treatment in multi-medicated patients presenting multiple co-morbidity factors. Rare cases of liver failure have also been reported. These cases underscore the importance of monthly monitoring of liver function throughout the bosentan treatment and the need to follow the above recommendations

The sponsor evaluates the expected or unexpected aspect of the serious adverse event using the SmPC and ascertains any possible implication of the treatment. The sponsor should declare all unexpected serious adverse effects to the European pharmacovigilance database (Eudravigilance), the French health authority (ANSM), the independent ethics committee and the investigators.

### Frequency and plans for auditing trial conduct {23}

The trial could be audited by the principal funder, the French Ministry of Health.

### Plans for communicating important protocol amendments to relevant parties (e.g. trial participants, ethical committees) {25}

The coordinating CRA and coordinating principal investigator are responsible for communicating important information concerning the trial, including any protocol amendments, to all parties concerned.

### Dissemination plans {31a}

Our objective is to publish the results of the trial in a peer-reviewed scientific journal and the result will also be disseminated via international conferences and/or seminars. The results will be reported in accordance with the CONSORT recommendations for randomised trials.

